## PREAMBLE

This study will be conducted in the context of an academic environment as part of the course requirements for the EPI301 Introduction to Epidemiology graduate level course, in the Fall 2022 semester, at the University of Zurich, Zurich, Switzerland.  
Some aspects of this Clinical Study Protocol are illustrative in nature.

## LIST OF ABBREVIATIONS

|        |                                                      |
|--------|------------------------------------------------------|
| AE     | Adverse Event                                        |
| BI     | Blinding Index                                       |
| CEC    | Cantonal Ethics Committee                            |
| CRF    | Case Report Form                                     |
| eCRF   | Electronic Case Report Form                          |
| EBPI   | Epidemiology, Biostatistics and Prevention Institute |
| GCP    | Good Clinical Practice                               |
| ICH    | International Council on Harmonization               |
| ISF    | Investigator Site File                               |
| KEK    | Kantonale Ethikkommission                            |
| LBP    | Low Back Pain                                        |
| MSK    | Musculoskeletal                                      |
| MT     | Manual Therapy                                       |
| PI     | Principal Investigator                               |
| RCT    | Randomized Controlled Trial                          |
| REDCap | Research Electronic Data Capture                     |
| ROM    | Range of Motion                                      |
| SAE    | Serious Adverse Event                                |
| SNCTP  | Swiss National Clinical Trial Portal                 |
| SOP    | Standard Operating Procedure                         |
| TMF    | Trial Master File                                    |

## **1 ETHICAL AND REGULATOR ASPECTS**

Before the start of the study, the protocol, proposed participant information and consent forms, as well as other study-specific documents would be submitted to a properly constituted Competent Ethics Committee (CEC) in agreement with local legal requirements, for formal approval or formal justified exemption, if applicable.

Since this blinding feasibility trial involved an intervention that is neither a cure, a transplant product, nor a transplant, it would be expected to fall into the low-risk category, Category A. The clinical study would only begin once approval from the CEC has been received.

### **1.1 Study Registration**

This study will be conducted in the context of an academic environment and will therefore not be formally uploaded to a registry. However, if the study were to be registered, the following registries would be useful: Swiss National Clinical Trials Portal (SNCTP) and [clinicaltrials.gov](https://clinicaltrials.gov).

### **1.2 Competent Ethics Committee (CEC)**

For the purposes of this study, the Kantonale Ethikkommission (KEK) of the Canton of Zurich would serve as CEC.

### **1.3 Ethical Conduct of the Study**

The study will be carried out in accordance with principles outlined in the current version of the Declaration of Helsinki, Good Clinical Practice (GCP) issued by International Council on Harmonization (ICH), and Swiss competent authority's requirements.

### **1.4 Declaration of Interest**

The authors have no competing interests to declare.

### **1.5 Participant Information and Informed Consent**

All study participants will receive a detailed participant information and consent form. The nature of the study, its purpose, the two trialed interventions, expected duration, potential risks, and any potential discomfort will be explained therein. All information will be provided without compromising the primary objective of evaluating blinding success. Although conceptualized in the context of a graduate-level class at the University of Zurich (Introduction to Epidemiology, EPI301, Fall 2022), participation in the proposed study is voluntary and participants can withdraw at any time. Completed formal informed consent forms are required in order to proceed with study participation.

### **1.6 Participant Privacy and Confidentiality**

The investigators are responsible for treating all information related to the study and the compiled data with strict confidentiality. No information will be distributed to entities not directly involved with the study. Data generation, transmission, archiving, and analysis of personal data within this study strictly follow the current Swiss legal requirements for data protection. Non-participation or withdrawal will not entail any disadvantages.

All medical information obtained for this study is considered confidential and disclosure to third parties is prohibited. Participant confidentiality will be further ensured by using participant identification codes that correspond with intervention data in electronic files, following a well-defined standard operating procedure (SOP).

Data generated as a result of this study will be made available for inspection on request by the assigned trial monitors and by the KEK.

## 2 INTRODUCTION

Methodological research efforts have focused on improving mechanisms and advancing techniques for blinding and allocation concealment processes in pharmacological trials, however maintaining such standards in high-quality randomized controlled clinical trials (RCTs) for non-pharmacological interventions has proven difficult. The concept of blinding describes the ignorance of study participants and/or study investigators to allocated intervention arms *during* the entire study period, while allocation concealment specifically describes the allocation of participants being concealed *before* inception of the study. Bias can happen at different stages of study execution; however effective blinding can minimize their occurrence. Exemplary types include misclassification bias (i.e., bias resulting from wrongful allocation of participants to intervention arms), performance bias (i.e., bias resulting from knowledge of applied interventions in either study investigators or participants), or detection bias (i.e., bias effects during outcome measurements).

Clinical trials of manual therapy (MT) interventions, although considered the reference standard for testing efficacy, face methodological challenges in the design of successful shams and blinding of assigned interventions. The use of a valid sham as a comparator in explanatory trials aims to discriminate specific from non-specific effects (i.e., contextual, not depending on the intervention itself) and mitigate performance, ascertainment, information, and other biases. Despite consensus on the ideal design of credible shams in physical interventions for pain and the proposal of some creative sham interventions (i.e., detuned laser therapy or ultrasound, deactivated instruments, low-velocity maneuvers in alternative body areas), few state-of-the-art clinical trials have assessed successful intervention blinding between active and control participants. This trend becomes more surprising when considering emerging evidence supporting the idea that clinical trials of MT with inadequate consideration of blinding tend to systematically magnify the effect of active interventions, thus compromising their overall internal validity and study quality.

To increase the reliability of MT RCTs, proposing an indistinguishable and potentially non-identifiable control intervention that mimics the active intervention without the specific active element and expected therapeutic effect is relevant. Assessing the blinding success of this intervention is also pertinent prior to the start of a trial, since post hoc blinding assessment may be confounded by intervention effects or hunches regarding intervention assignment. Given the multiple proposed mechanisms of MT and the well-established biopsychosocial nature of pain, the development of credible sensory experiences that mimic active interventions in the field of manual medicine, without therapeutic intent and presumed effects (i.e., inertness), remains an ongoing research priority.

This feasibility trial aims to assess the blinding success of an active MT intervention and a developed sham intervention (i.e., control intervention). This assessment will include i. participant level of certainty regarding the assigned intervention arm, ii. the description of self-reported factors contributing to perceived intervention arm allocation, and iii. level of certainty in outcome assessors regarding participant intervention arm allocation.

### 2.1 Background and Rationale

Musculoskeletal (MSK) conditions are a rising non-communicable disease and leading cause of years lived with disability (YLD). Non-specific low back pain (LBP) represents the most prevalent diagnosis in all age groups, being one of the main reasons for healthcare-seeking and productivity loss in developed countries. Among younger populations, including college-age students, LBP is especially associated with psychosocial factors. In Switzerland, LBP alone accounts for approximately 2.6 billion euros in direct costs, representing 6% of total healthcare expenditures and raising a need for specific treatment.

Although the use of anti-inflammatory drugs is habitual in the treatment of LBP, multiple non-pharmacological interventions are stated as first-line treatment options. Among conservative treatment options for LBP, MT remains a non-invasive and cost-effective option, best when used within the context of multimodal care, which tends to include different forms of exercise and psychological interventions. Several plausible mechanisms of MT have been proposed. First, at the level of the peripheral nervous system, mechanical stimuli have been suggested to produce some tissue responses (changes in inflammatory mediators) that can, in turn, produce overall decreased spasms and increased range of motion (ROM). Second, at the level of the spinal cord (central

nervous system), MT has been proposed as a facilitator of certain neuromuscular responses (motoneuron pool, afferent discharges that favor muscle activity), and hypoalgesia (through temporal summation, selective blocking of neurotransmitters). Third, regarding pain-related brain circuits, there are suggested pathways with modulatory effects involving specific brain sections related to stress management such as the amygdala. These modulatory circuits may play a role in subsequent non-specific responses of MT including placebo/expectation, psychological measures (fear, catastrophizing, kinesiophobia), endocrine responses (B-endorphins and endocannabinoid response), and autonomic response (skin temperature, skin conduction, cortisol levels, heart rate).

To elucidate the true efficacy of the active element in MT strategies for back pain and MSK pain in general, the development of validated sham MT interventions with a known degree of blinding success is crucial. This will allow for improved designs of future high-quality controlled randomized controlled trials.

## **2.2 Justification of Study Intervention**

MT, which typically encompasses manipulation, massage and mobilization of joints and soft tissue, may be indicated for acute and chronic LBP. MT can be delivered as a stand-alone intervention or in combination with other interventions as an adjunctive yet first or second-line option for LBP management. A standard MT trial of care for a given MSK complaint may involve multiple sessions (i.e., 6–10) for a period of four to six weeks, each of which requires at least 10 minutes to be delivered. There is limited evidence to suggest a definitive optimal frequency or ideal session duration for MT interventions. Pragmatic clinical decisions often take place on an individual basis and consider factors beyond clinical evidence such as patient values and clinician expertise.

## **2.3 Explanation for Choice of Comparator Intervention**

In the context of this trial, the comparator intervention (i.e., control intervention) aims to assess the feasibility and suitability of a sham MT intervention, with respect to blinding success. As exemplified in previous similar studies conducted by Nyugen et al. (2021) and Tavares et al. (2017), the choice of a sham intervention is necessary to control for the placebo effect. The yielded results in blinding success can be used to inform future explanatory trials in the field of MT.

The choice of comparator intervention is further detailed under section 7 *STUDY INTERVENTION*.

## **2.4 Risk / Benefits**

Both the defined active and control intervention involve mobilization of defined paraspinal soft tissue regions of the back. Due to the gentle, non-invasive nature of the interventions, potential side effects, if any, are expected to be mild and temporary and may include localized redness, transient muscle soreness, and self-resolving altered local sensitivity.

Potential benefits of MT may include improvement of different dimensions of low back function (i.e., ROM, self-perceived flexibility). However, since we will administer a brief MT intervention in our feasibility study, the effect on low back function is uncertain.

## **2.5 Rationale for Chosen Study Population**

The study population is graduate students at the University of Zurich with health-related educational backgrounds. Our study population is limited to 26 students enrolled in the EPI301 course for the Fall 2022 semester. Studies have found that LBP among university students is highly prevalent partly due to prolonged sitting, poor ergonomics, carrying heavy bags, and stress. A study by Anggiat et al. (2018) found a reported LBP incidence of 70% in students, with the majority of surveyed participants reporting prolonged sitting of more than three hours per day. Similar results were observed in a large cross-sectional study of health science students, in which approximately 60% reported lifetime prevalence and 50% reported a 1-year prevalence of LBP. This study additionally found a significant link between sedentary behavior and LBP prevalence.

### 3 STUDY OBJECTIVES

To assess blinding among participants assigned to either an active or sham-control MT intervention immediately after a one-time intervention session, and to also assess blinding among outcome assessors.

#### 3.1 Primary Objective

The primary objective of this study is to compare an active and control intervention regarding blinding success in participants.

#### 3.2 Secondary Objectives

The secondary objectives are (1) to assess blinding success in outcome assessors of the study, (2) to identify factors contributing to perceived intervention arm allocation in study participants as well as outcome assessors, and (3) to explore the effect of two applied interventions on low back function.

### 4 STUDY OUTCOMES

#### 4.1 Primary Outcome

The primary outcome of this study is blinding success, as measured by the Bang blinding index (BI). The planned assessment of this outcome is detailed under *0 Assessment of Primary Outcome*.

#### 4.2 Secondary Outcomes

The secondary outcomes of the present study are (1) blinding success in outcome assessors as measured by the Bang BI, and blinding success in both participants and outcome assessors as measured by another validated blinding assessment index—the James BI; (2) different dimensions of low back function; and (3) contributing factors to perceived intervention arm allocation. The planned assessment of these outcomes is detailed under *0 Assessment of Secondary Outcomes*.

#### 4.3 Safety Outcomes

We do not anticipate any risks associated with participation in this study. However, safety outcomes will be evaluated during the trial and participants will have the opportunity to contact the principal investigator to report adverse events at any time. More information on anticipated safety outcomes and their handling during trial can be found under *8.3 Assessment of Safety Outcomes*.

### 5 STUDY DESIGN AND COURSE OF STUDY

#### 5.1 General Study Design and Justification of the Design

This feasibility trial is a two-arm parallel randomized controlled trial (1:1 allocation ratio) that compares an active and control intervention in terms of blinding success. Based on pre-piloting, enrolled participants will be able to complete outcome assessments and interventions in approximately ten minutes. Individual participants will be assigned a specific time slot during the day of the trial execution. An initial intake form will be filled out by study participants via Research Electronic Data Capture (REDCap 12.5.14) the day before the clinical trial is conducted.

The two tested interventions target the back region and pose minimal risks, even for asymptomatic populations. The active intervention will be operationalized as passive soft tissue mobilization of the lumbar paraspinal muscles with the patient laying in a prone position. The control intervention will be operationalized as a series of bilateral light touches that follow the rhythm of deep breathing of the participant applied at the level of the scapular region and more caudally to the level of the lower part of the rib cage (T12). The control intervention is not known to have any beneficial effects and closely resembles a validated MT sham proposed, thus providing reasonable structural equivalence with respect to the active intervention.

The study population will be restricted to a convenience sample of graduate students from the University of Zurich. There is limited preliminary information regarding the sociodemographic characteristics of this study population and how it may relate to the general graduate student population of Switzerland. It is also unclear how the underlying characteristics of this student population may influence our blinding assessment.

To ensure blinding of participants, outcome assessors and data analysts, the study will be conducted in two different rooms at the University of Zurich. In addition, two different REDCap accounts will be created to prevent accidental unblinding of outcome assessors and data analysts within the REDCap system.

We will perform stratified blocked randomization, with varying permuted blocks (block sizes not disclosed to ensure concealment of allocation), to achieve unconditional exchangeability between the two intervention groups. The stratification variable will be self-reported previous experience with MT coded as a binary variable. A computer-generated randomization sequence created by an EBPI biostatistician not otherwise involved in the trial will be used to randomly assign participants to the active and control intervention groups in a 1:1 ratio. Patients will be allocated to intervention groups through central, web-based randomization (via REDCap) once the demographic data and eligibility criteria are entered in an electronic form and informed consent is obtained. Only trial intervention providers will have information on the assigned intervention.

## **5.2 Study Duration and Study Schedule**

SENSATE will be performed in a single academic center in Zurich (University of Zurich, Main Building) and on a single day (November 8, 2022). For feasible completion, two different rooms will be dedicated to the successful completion of the present study, with further logistic decisions made in accordance with the central organization bodies. The study schedule with the measurements and time points can be found in the Study Procedures Section. Data analysis and course report will be completed by November 14, 2022.

## **5.3 Methods of Minimizing Bias**

To maximize the internal validity of this study and to control for confounding, we will apply multiple methodological approaches. First, we will use stratified randomization to balance the active and control intervention arms regarding the main anticipated confounder (i.e., experience with MT) and to facilitate subgroup analysis. Furthermore, participants, outcome assessors, data analysts and investigators will be blinded to the intervention. Blinding success will be quantitatively assessed. Due to the inherent physical nature of the interventions, the interventionists (i.e., MT providers) cannot be blinded. However, the randomly allocated intervention will not be revealed to them until the time of intervention delivery. The information will be provided on the REDCap platform at the moment the participant enters the intervention room. We will follow standardized instructions from predefined SOPs to ensure that participants in both groups will receive the intended intervention. Furthermore, the SOPs also define the measurement procedure to ensure that the measurement in both groups is applied using the same measures and the same process. Statistical methods to reduce bias from missing data and drop-outs are described in section 10.3 *Handling of Missing Data and Drop-Outs*. Finally, we will follow our predefined data analysis plan as described in section 10.

### **5.3.1 Randomization**

Stratified randomization (1:1 allocation ratio) will be performed using previous experience with MT (yes/no) as the stratification variable. This will be done, as we assume this characteristic may play a role when it comes to perceptions about assigned intervention. Varying permuted blocks (block sizes not disclosed to ensure allocation concealment) will be generated by an external biostatistician, and concealment of the list will be achieved electronically in REDCap.

## **6 STUDY POPULATION**

Our study population is made up of health-related graduate students at the University of Zurich. Our study population is limited to 26 students enrolled in the EPI301 Introduction to Epidemiology graduate-level course

for the Fall 2022 semester. Further information regarding our study population can be found in Section 2.6 *Study Population*.

### **6.1 Eligibility Criteria**

Inclusion criteria:

- 18 years of age and older
- Students enrolled in EPI301 course at UZH (Fall 2022 Semester)

Exclusion criteria:

- Presence of serious disease of the back (e.g., cancer, severe scoliosis, inflammatory disease, infection)
- Previous spinal operation
- Current pregnancy or breastfeeding
- Inability to lie prone (on the belly)

### **6.2 Recruitment and Screening**

All students enrolled in the “EPI301 Introduction to Epidemiology” course are eligible for participation. Participant eligibility will be determined based on the self-disclosure regarding potential exclusion criteria determined on the day of the study. Study participants will incur no charge upon enrollment into the study nor receive any financial reward for participation.

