#### ***B) Control intervention***

In a standardized deep breathing sequence, patients are instructed to deeply inhale and exhale for 2x3x3 repetitions. Light rhythmic pressure is applied to the thoracic region during expiration with both hands placed on the back, starting at the level of the scapula. The position is adjusted in caudal direction after each repetition. The length of the sham intervention equals the active intervention.

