### 10.1 Sample Size Consideration

A precision-based approach has been used to consider sample size (i.e., width of the 95% CI) for the Bang BI estimates rather than statistical power given this is a methodological feasibility randomised trial. We propose to estimate the Bang BI for each group and present a 95% CI for each mean BI point estimate. For a sample size of 26 participants in total (the maximum given our limited class size), the 95% CI will be the observed BI estimate  $\pm 0.315$  points (0.63 points width of the 95% CI) for the primary outcome measure of the group-specific Bang BI, according to Thompson's method (Eq 1) as described by Landsman and colleagues in their study on sample size calculations for blinding assessments. The small class size will inherently limit the precision of our

estimated BI. Ideally, we would want to carry out this trial in a larger study population of approximately 40 participants (20 per group) for a 0.50 points width of the Bang BI 95% CI.

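### The participants are classmates on the course that runs the trial, seen in slots on one day, and the protocol text has no guard against outside information biasing the primary blinding index

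*Protocol*

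**What the plan says.** - **Course setting.** The Preamble says the study is conducted "as part of the course requirements for the EPI301 Introduction to Epidemiology graduate level course".
- **Sampling frame.** Section 2.5: "Our study population is limited to 26 students enrolled in the EPI301 course for the Fall 2022 semester". Section 6.2 adds: "All students enrolled in the “EPI301 Introduction to Epidemiology” course are eligible for participation". The exclusion criteria in Section 6.1 are medical or physical (serious back disease, spinal operation, pregnancy or breastfeeding, inability to lie prone).
- **Scheduling.** Section 5.1: "Individual participants will be assigned a specific time slot during the day of the trial execution". Section 5.2 fixes a single day, 8 November 2022, and Section 8.1 gives about ten minutes from T0 to T1.
- **The arms.** Section 7.1.1 describes deep soft tissue work at three lumbar points on each side for the active arm. For the control arm it says: "In a standardized deep breathing sequence, patients are instructed to deeply inhale and exhale for 2x3x3 repetitions", with light pressure on the thoracic region.
- **Safeguards.** Section 5.1: "To ensure blinding of participants, outcome assessors and data analysts, the study will be conducted in two different rooms at the University of Zurich". Two REDCap accounts protect assessors and analysts. Section 1.5 says information will be given in a way that does not compromise the blinding objective. Section 5.3 lists stratified randomisation, blinding, late disclosure to the interventionists, and SOPs.
- **Outcome.** The primary outcome is the Bang index from the participant's guess at T1 (Sections 4.1 and 8.2). Success is a point estimate from -0.2 to 0.2 (Section 10.2, Primary Analysis). An open-ended item asks for the reason behind the guess (Table 1).

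**The concern.** The trial exists to learn whether the sham itself keeps participants from knowing their arm. That reading requires the guess to come from the session. Two features let in information from elsewhere.

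1. **Talk between classmates.** The arms differ in body region, depth of touch and breathing instruction, which a short description can convey. Someone seen early can describe the session to someone seen later. Two rooms and two REDCap accounts are not described as keeping treated and waiting students apart.
2. **Prior knowledge.** The course that provides the participants also runs the trial. The eligibility rule as written would admit a student who helped design, run or analyse it, or who has read the protocol or SOP. Such a student knows which manoeuvre carries the label 'active'.

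The index cannot separate these sources from a weak sham. Section 2.3 intends the result to inform later explanatory trials, so a biased index would carry over into the choice of sham.

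**Working it through.** **Inputs.** Protocol: 26 students (Sections 2.5 and 6), 1:1 allocation (Section 5.1), hence 26/2 = 13 per arm if all join; success range -0.2 to 0.2 (Section 10.2). Assumed, because the documents give no figure: the number k of fully informed participants in an arm, the share answering 'do not know', and the index BI0 among the uninformed.

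**The plan's own figure.** Section 10.1 states a half-width of 0.315 at 26 participants by Thompson's method. With the worst-case multinomial constant 1.2736 (three categories), d = sqrt(1.2736/13) = 0.313, which agrees within rounding. This confirms 13 per arm as the planning basis. The concern does not depend on it.

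**Index.** Reading the proportion in the Section 10.2 formula as the share correct among those in the arm who name an arm, the formula reduces to BI = (correct - incorrect)/13.

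**Expected shift.** If k of 13 always answer correctly and the others have index BI0:

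E[BI] = k/13 + (1 - k/13) x BI0

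With BI0 = 0, each informed participant adds 1/13 = 0.077, and three give 3/13 = 0.23, beyond the upper limit of 0.2.

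**Chance of meeting the criterion, no 'do not know' answers.** BI = (2c - 13)/13 for c correct guesses, so -0.2 to 0.2 requires c = 6 or 7. The 13 - k uninformed participants guess at 0.5.

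| k | E[BI] | Correct among uninformed | P(criterion met) |
|---|---|---|---|
| 0 | 0.00 | 6 or 7 of 13 | (1716 + 1716)/8192 = 0.42 |
| 1 | 0.08 | 5 or 6 of 12 | (792 + 924)/4096 = 0.42 |
| 2 | 0.15 | 4 or 5 of 11 | (330 + 462)/2048 = 0.39 |
| 3 | 0.23 | 3 or 4 of 10 | (120 + 210)/1024 = 0.32 |
| 5 | 0.38 | 1 or 2 of 8 | (8 + 28)/256 = 0.14 |

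**With 30% 'do not know' among the uninformed** (simulation, 200,000 runs): 0.59 for k = 0, 0.41 for k = 3, 0.15 for k = 5.

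**The other direction.** Suppose uninformed participants tend to guess wrongly, BI0 = -0.3, with 20% 'do not know'. Then k = 3 gives 3/13 + (10/13) x (-0.3) = 0.231 - 0.231 = 0.00. By simulation, the chance of meeting the criterion rises from 0.29 to 0.65. Here the informed participants make blinding look better than it was.

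**The case against.** Several points on the other side are sound and limit the claim.

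- **Absence is only partly checkable.** A request not to discuss the session could sit in the consent form or the SOPs, which are not shown. A reader might infer that nothing stops participants from learning about the arms. The documents support only that the protocol text states no such measure.
- **Hearsay is not full knowledge.** An early participant is also blinded and can pass on a description but not the label. The listener must still judge which procedure is active, and the classmate's opinion may be wrong. Section 1.5 also has the two interventions explained to everyone. The stronger reading, that any informed participant answers correctly however credible the sham, fits only someone who knows the label.
- **Protocol knowledge is a possibility.** A reader might infer that participants wrote or ran the trial. No section says so; the eligibility rule merely leaves it open.
- **The upper tail alone overstates the effect.** On the same model the chance of an index above 0.2 rises from 2380/8192 = 0.29 (k = 0) to 638/1024 = 0.62 (k = 3). The criterion is two-sided, and the chance of meeting it falls only from 0.42 to 0.32. Even without outside information, an arm with random guessing misses the range 58% of the time.
- **The reason for the guess is recorded.** The open-ended T1 item is planned and analysed thematically, so hearsay may come to light. It does not enter the index, however, and it does not ask about outside sources.

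Section 5.1 also admits that the influence of this student population on the blinding assessment is unclear, but attaches no remedy. What stands after these points is the gap itself: eligibility, scheduling and the listed safeguards leave both routes open.

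**Conclusion.** The point holds as a correctable weakness in design. Following Section 6 as written can bias the primary endpoint, and the sign of the bias is not fixed. Label knowledge pushes the index toward +1; hearsay acts more weakly and either way; and where uninformed guesses run against the truth, outside knowledge can bring a poor result inside the success range.

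The figures of 0.077 per fully informed participant and 0.42 falling to 0.32 with three are an upper case. They rest on 13 per arm, no 'do not know' answers, certain knowledge among the informed and random guessing otherwise. Three per arm would mean six of 26 students, and the documents give no basis for that or any other number. The documents do not show that contamination will occur, or that a good sham will be rejected because of it.

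**What to change.** 1. **No discussion.** In Section 8.4, ask each participant at consent, and again on leaving the T1 station, not to discuss the session until the last slot is finished. Give no feedback on allocation before then. If the consent form or SOP already says this, state it in Section 5.3.
2. **Eligibility.** Add to Section 6.1 an exclusion for students with a role in designing, running or analysing the trial, or who have read the protocol or the intervention SOP. Amend Section 6.2 to match, and restate the maximum sample in Sections 2.5, 6 and 10.1.
3. **One T1 item, placed after the guess.** It must be limited to sources other than the study information, since otherwise everyone could properly answer yes. For example: *Apart from the study information given to you, did you learn before your session from another person or document what is done in either intervention?* Report the Bang index per arm also without the yes answers, as a sensitivity analysis beside the intention-to-treat result.

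**Cost.** Two spoken sentences, one exclusion criterion, one REDCap item and one extra analysis. The eligible number may fall below 26. By the method of Section 10.1, 12 per arm gives sqrt(1.2736/12) = 0.326 and 11 per arm sqrt(1.2736/11) = 0.340, against 0.313 at 13, a slight loss of precision.
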